**Fig 1 pone.0280686.g001:**
[figure not shown]
Schedule of enrolment, intervention, and assessments.

This study will be a four-arm cluster randomized controlled trial study with three phases and a twelve-month follow-up by country stratification. This study will evaluate the effectiveness of the gamified live feedback intervention on children’s handwashing behaviour, self-efficacy, and motivation in three different phases: the baseline, intervention, and post-intervention phases. In Finland, there will be a twelve-month follow-up after the baseline phase. This study will consist of four groups, the control group, and three different intervention groups. All the groups will have automated monitoring systems installed before the start of the baseline phase and will be available in all phases. The system will be de-installed after the post-intervention phase.

During the baseline phase, all the groups will have no screen activity. During the intervention phase, the control group will have no screen activity. The intervention A group will have a screen display providing handwashing instructions but no reward, and the intervention B and C groups will receive handwashing instructions and rewards from the screen display. During the post-intervention phase, all the groups will have no screen activity except the intervention C group which will receive handwashing instructions but no reward (Fig 2).

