### Sample size

The sample size is calculated based on the significant effects found during the pre-study. In the pre-study, 10,000 handwashing events were recorded over a period of 42 days in a treatment group (n = 82 children in two clusters) and a control group (n = 53 children in two clusters). Using Cohen’s power analysis with f^2^ = 0,35 (large effect size) and power level of 0.8 and 2 predictors and a probability level of 0.05 leads to n = 31. However, since randomization is on a cluster level, the n must be increased. With the ICC from the pre-study of 0.062, and estimated cluster size (size of each kindergarten) of 40 children, we calculate the design effect:

D=1+(m−1)*ICC=1+(40−1)*0.062=3.418

Thus, we need to increase the sample size by 3.418 compared to individual randomization, due to cluster randomization leading to 106 participants (n = 31 * 4.418 = 106). With the assumption of a cluster size of 40 children per kindergarten, this leads to three kindergartens that need to participate in the study. Each kindergarten represents one cluster and gets assigned to be the control, the intervention A, B, and C groups. Two intervention groups will be covered by one cluster.

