### Randomization

The cluster randomization will be at the kindergarten level. Kindergartens will be randomly assigned to control or intervention groups by two researchers that are not members of the research team and are stratified by country. One kindergarten serves as one cluster. Simple randomization will be used which will be drawing lots, where each cluster will be assigned a number in a piece of paper. The parents will enrol their children for participation in the study within the time set through the website link provided and email.

No information will be given regarding the allocation. Allocation will be about four weeks before the start of the baseline phase and will be conducted by the two non-member researchers. They will generate the allocation sequence, enroll the participants, and assign them to control or intervention groups. There will be complete concealment of the allocation from the members of the research team and the participants, to exclude the possibility of predicting the next allocation [33].

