### Data analyses

Data will be analysed using qualitative and statistical methods. All eligible participants will be included in the analysis. The statistical analyses will be performed with R. The categorical and numerical data will be analysed using one-way analysis of variance (ANOVA). Qualitative analysis will be presented thematically [42].

For the measurement data from the system:

Data pre-processing: Data will be investigated where water and soaping data are combined to single handwashing procedures. Data points that are not valid (outside of kindergarten opening hours) will be removed. The descriptive statistics of the clusters, randomization checks, ICC (intracluster correlation) will be calculated. The data will be analyzed using linear fixed-effect regression model for panel data, and dependent variable soaping time. The four groups will be compared in baseline, intervention, and post-intervention phases.

For the survey and staff interview data:

The comparison among the groups will be implemented using random effects regression, allowing for the clustered nature of the data, and adjusted using the covariates of the adjusted analyses (when a small number of clusters are present) [43]. Simple bias analysis will be used to quantify the uncertainty of the biases such as confounding variables [33]. The qualitative results of the survey and kindergarten staff interview will be analysed and compared thematically. The four groups will be compared after intervention phase.

For the children interview and observation data:

The analyses will be compared among groups based on the complete data only. The comparative analyses approach used to calculate the observation, survey, and staff interview will be used. The self-efficacy measurement scale will be developed and evaluated for its psychometric properties [44,45]. The qualitative result of the observation and interviews will be analysed and compared thematically [42]. Children who will participate the interview at one time point will be considered as missing data, these will be excluded from the analysis. The four groups will be compared in baseline, intervention, and post-intervention phases.

For the sickness day data:

The total sick leave days are compared among the groups one year before and after the start of the baseline phase.

The statisticians of the two universities will validate the statistical results of the data.

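### With three kindergartens for four arms, the planned random effects regression cannot estimate kindergarten variance, so single-time-point comparisons between arms in different kindergartens are not cluster-adjusted

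*Protocol article*

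**What the plan says.** The Data analyses section of the protocol article assigns one method to the parent survey and the staff interviews, namely: "The comparison among the groups will be implemented using random effects regression, allowing for the clustered nature of the data". Its only provision for few clusters is that the comparison is "adjusted using the covariates of the adjusted analyses (when a small number of clusters are present"). For the child interviews and observations it adds: "The comparative analyses approach used to calculate the observation, survey, and staff interview will be used".

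The Randomization section fixes the unit: "The cluster randomization will be at the kindergarten level". The Sample size section concludes that "this leads to three kindergartens that need to participate in the study", and continues: "Each kindergarten represents one cluster and gets assigned to be the control, the intervention A, B, and C groups". It closes with "Two intervention groups will be covered by one cluster". The trial has four arms.

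On timing, the Data collection section places the parent survey in the last intervention week. Staff interviews take place in that week and in the first post-intervention week. Child interviews and observation sessions take place at the end of each of the three phases.

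**The concern.** A random kindergarten effect allows for clustering only if the data show how much kindergartens differ when they receive the same treatment. That requires at least one arm with more than one kindergarten, and the text provides none. The difference between two arms in different kindergartens is also the difference between those kindergartens, and the model cannot separate the two.

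The software may still print standard errors and p-values. They would be reported as allowing for clustering when they are either those of unclustered data or a product of where the optimiser stopped. At stake are the between-arm conclusions on hand hygiene at home and on staff-rated behaviour, together with any comparison of child interviews or observations made at one phase only.

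**Working it through.** **1. The plan's own figures.** Inputs from the Sample size section: f² = 0.35, power 0.80, 2 predictors, 5% level, ICC 0.062, 40 children per kindergarten.
- Power from the noncentral F distribution is 0.804 at n = 31 and 0.789 at n = 30, so n = 31 is reproduced.
- Design effect: 1 + 39 × 0.062 = 3.418.
- 31 × 3.418 = 105.96, so 106 is reproduced. The printed multiplier 4.418 would give 136.96; it is a misprint that does not affect the total.
- 106/40 = 2.65, rounded up to three kindergartens.

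**2. Degrees of freedom.** Let X hold the arm indicators and Z the kindergarten indicators. The between-kindergarten degrees of freedom are rank[X, Z] − rank[X].

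| Layout | df |
|---|---|
| 3 kindergartens, 3 conditions | 0 |
| 3 kindergartens, 4 arms, one kindergarten split between two arms | 0 |
| 4 kindergartens, 4 arms | 0 |
| 6 kindergartens, 3 conditions | 3 (2 after a country effect) |

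Kindergarten-level covariates are aliased with arm, and child-level covariates add no between-kindergarten degrees of freedom. The covariate provision therefore does not help.

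**3. What the software would return.** Simulated data, 40 children in each of three kindergartens under three conditions, with r = kindergarten variance / within-kindergarten variance:

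| r | REML log-likelihood | ML log-likelihood | SE of arm contrast |
|---|---|---|---|
| 0 | 10.4755 | 17.94 | 0.195 |
| 0.01 | 10.4755 | 17.43 | 0.231 |
| 0.066 | 10.4755 | 16.00 | 0.372 |
| 1 | 10.4755 | 12.37 | 1.249 |
| 10 | 10.4755 | 8.95 | 3.905 |

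The restricted likelihood is flat, so it supports no particular standard error. The ordinary likelihood is highest at zero, which returns the standard error that ignores kindergarten. With one kindergarten split between two arms the pattern is the same, except that the contrast between those two arms keeps an SE of 0.286 at every r.

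**4. Size when the variance is set to zero.** The residual then estimates only the within-kindergarten variance, so the true variance of a contrast exceeds the printed one by the factor 1 + m × ICC/(1 − ICC). Here m is the number of respondents in each of the two arms, or their harmonic mean if unequal. Type I error = 2 × [1 − Φ(1.96/SE ratio)].

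| m | ICC | Variance factor | SE ratio | Type I error |
|---|---|---|---|---|
| 26.5 (106/4) | 0.062 | 2.75 | 1.66 | 24% |
| 40 | 0.062 | 3.64 | 1.91 | 30% |
| 40 | 0.01 | 1.40 | 1.18 | 10% |
| 40 | 0.10 | 5.44 | 2.33 | 40% |

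An arm of 20 in a shared kindergarten against an arm of 40 has harmonic mean 26.7 and falls at the 24% end.

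**5. Change from baseline.** Generalised least squares with 36, 35, 17 and 18 children per arm (the last two in one kindergarten), two phases, and an assumed child variance of 0.4 and residual variance of 0.6. As the kindergarten variance goes from 0 to 5, the SE for arm A against control runs from 0.237 to 3.17 at the later phase alone. For the change from baseline it stays at 0.260. A constant kindergarten effect cancels. A kindergarten-by-phase effect does not cancel and is just as inestimable.

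**The case against.** A reader might infer that every secondary outcome is affected, and that H4a and H4b on self-efficacy are decided with a false-positive rate near 30%. The documents do not support that. Child interviews are collected in all three phases, the groups are compared in all three, and both hypotheses speak of an increase. If they are tested as change from baseline, step 5 shows that a constant kindergarten effect drops out. The Data analyses section does not say which contrast is meant, so the error rates in step 4 belong to post-only comparisons.

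A reader might also want to inflate every arm contrast. That would be wrong for the two arms that share a kindergarten, because their contrast is within-cluster.

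Three further objections stand in part.
- The ICC of 0.062 comes from a pre-study of recorded handwashing events. Nothing ties it to three-point child scales or to parent and staff ratings, and the number of staff per kindergarten is not given. A range is therefore needed.
- Randomization is stratified by two countries and the allocation flowchart is not shown, so more kindergartens may take part. If there were three per country (an assumption), the model would be estimable on only 2-3 degrees of freedom. The text, however, says three for the study.
- The system-recorded primary outcome uses a different model and is outside this point.

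**Conclusion.** The point holds within those limits. Under the stated three kindergartens for four arms, and equally with one kindergarten per arm, the kindergarten variance is not identified for single-time-point contrasts between arms in different kindergartens. This covers the parent survey and staff interviews for certain, and any post-only comparison of child interviews or observations. For these the analysis does not deliver the allowance for clustering that it claims.

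The loss of identification follows from the layout alone. The size, about 24-30% instead of 5%, rests on the variance being set to zero, on the pre-study ICC carrying over to these scales, and on about 27-40 respondents per kindergarten. Staff numbers may be quite different.

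**What to change.** In the Data analyses section:
1. Do not describe these results as cluster-adjusted by an estimated random effect.
2. For between-kindergarten, post-only contrasts, fix the kindergarten variance externally at ICC/(1 − ICC) times the within-kindergarten variance. This is the variance factor 1 + m × ICC/(1 − ICC), with the actual number of respondents as m. Use ICC 0.062 and a sensitivity range such as 0.01-0.15, and state that the intervals rest on this assumption.
3. Analyse child interview and observation outcomes as change from baseline with a child random effect, and add a sensitivity analysis for an assumed kindergarten-by-phase variance.
4. Leave the contrast between arms sharing a kindergarten uninflated.
5. Keep the estimated kindergarten random effect only if at least two kindergartens per arm take part, with a small-sample degrees-of-freedom correction.

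The cost is a change of wording and a few lines of R. Intervals for between-kindergarten post-only contrasts become about 65-90% wider at ICC 0.062 and m = 26.5-40.

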### Outcome measures

The primary outcome is the hand hygiene behaviour of the children. The system will measure the hand hygiene activities which includes the start time of extraction, water volume, water temperature, and end time of extraction; from these data, the following data will be derived: average flow rates, approximation of energy consumption, quality and duration of handwashing, and time stamp of soap used.

The secondary outcomes are self-efficacy, intrinsic motivation, hand hygiene behaviour at home from parents’ survey, hand hygiene behaviour in kindergartens from kindergarten staff, and hand hygiene behaviour in the kindergarten by observation sessions. Self-efficacy and intrinsic motivation will be measured from the children’s one-on-one interview, a three-point Likert scale with open-ended questions. The children will be asked easy and simple questions about their hand hygiene performance, self-regulation on motivation, emotional states, and decisional in performing handwashing. They will respond by pointing their answer from the three smiley faces (sad, neutral, and happy). Colourful smiley faces will be constructed to catch the attention of the children. Each question is followed by open-ended questions to explore their opinions regarding the topic asked and to support their answers. The children interview includes introduction of the interviewer and asking simple questions regarding their day or regular activities for the children to feel comfortable. The parent survey will be an electronic survey composed of five-point Likert and open-ended questions about the observed hand hygiene behaviour of the children at home. The kindergarten staff interview will also include five-point Likert and open-ended questions, evaluating the hand hygiene behaviour of the children in the kindergartens. The assistant researchers will observe the hand hygiene behaviour of the children during the handwashing activity in the kindergartens. Observation sessions will include a checklist consisting of the phases of handwashing, the checklist will follow the hand hygiene guideline of the United Nations Children Fund (UNICEF).

The tertiary outcome is the number of sick leave days of the children and kindergarten staff (applies in Finland) considering the seasonal change.

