### Data collection

This study will start in mid-year of 2022 and will last for a year. The data will be analysed using quantitative and qualitative methods. The child’s age and gender will be collected. The implementation phases and timeline of the data collection are shown in Figs 1 and 2.

The handwashing activity data from the system will be recorded every day during the baseline, intervention, and post-intervention phases. The parent survey data will be given and collected within the last week of the intervention phase. The kindergarten staff interview data will be collected during the last week of the intervention phase and right in the beginning week of the post-intervention phase to evaluate the observed effect of children’s hand hygiene behaviour and reactions towards the removal of the instructions and reward. The children’s observation sessions and interviews will be collected during the last weeks of the baseline, intervention, and post-intervention phases. The number of sick leave days will be collected from the sick leave records provided by the kindergarten staff one year before and after the start of the baseline phase.

The follow-up strategy will include sending updates of the study phases through email to the kindergarten managers and staff. The email includes the details of reminding how and when the participants will be contacted for follow-up. It will also include updates on the contact information of the participants.

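### Child interview and observation outcomes are limited to complete data and single-interview children are dropped, against the all-participants rule and with two-visit children left undefined

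*Protocol article*

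**What the plan says.** All of the analysis rules stand in the Data analyses section of the protocol article.

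- The opening paragraph sets a general rule without a stated limit: "All eligible participants will be included in the analysis".
- For the child interview and observation data: "The analyses will be compared among groups based on the complete data only".
- For the interviews, it then adds: "Children who will participate the interview at one time point will be considered as missing data, these will be excluded from the analysis".
- The comparisons planned for these data are by phase: "The four groups will be compared in baseline, intervention, and post-intervention phases".
- The child data reuse the approach that the section describes for parents' and staff responses: "The comparison among the groups will be implemented using random effects regression, allowing for the clustered nature of the data".

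Data collection sets three child assessments: observation sessions and "interviews will be collected during the last weeks of the baseline, intervention, and post-intervention phases". Outcome measures shows what depends on them: "Self-efficacy and intrinsic motivation will be measured from the children’s one-on-one interview". Both are secondary outcomes, as is hand hygiene seen in the observation sessions. Hypotheses H4a and H4b concern children's self-efficacy after the intervention phase and after the post-intervention phase.

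**The concern.** The general rule includes every eligible child; the two specific rules do not. The specific rules also fail to define each other. With three visits, complete data suggests all three, yet the deletion sentence names only children interviewed once. A child with two interviews is excluded on one reading and kept on the other, and an analyst could settle this after seeing the data.

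The deletion is also not needed. The groups are compared in each phase, so a child seen once has a valid observation for one planned comparison. Random-effects regression accepts incomplete records, and even a separate comparison at each phase could use that child.

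What is at stake is precision and possibly bias in the results for H4a and H4b. If the children who miss a visit differ in their earlier responses, and do so differently by arm, an unadjusted complete-case comparison can be shifted.

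**Working it through.** **The plan's own figure.** Sample size uses n = 31, ICC 0.062 and 40 children per kindergarten. The design effect is 1 + (40 − 1) × 0.062 = 3.418, and 31 × 3.418 = 105.96, so 106. This reproduces the stated total. The multiplier printed in the last step, 4.418, would give 137 and is a misprint. The calculation shows no allowance for missed assessments.

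**Loss of children and interviews.** The article gives no missingness rate, so assume that each of the three visits is missed independently with probability d.

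- Children with all three visits: (1 − d)³
- Children with exactly one visit: 3(1 − d)d²
- Share of collected interviews discarded under a strict three-visit rule: 1 − 3(1 − d)³ / [3(1 − d)] = 1 − (1 − d)²
- Share discarded if only single-visit children are dropped: 3(1 − d)d² / [3(1 − d)] = d²

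| Assumed d | All three visits | Of 106 | Interviews lost, strict | Exactly one visit | Of 106 | Interviews lost, single-visit rule |
|---|---|---|---|---|---|---|
| 5% | 85.7% | 91 | 9.7% | 0.7% | 1 | 0.2% |
| 10% | 72.9% | 77 | 19.0% | 2.7% | 3 | 1.0% |
| 20% | 51.2% | 54 | 36.0% | 9.6% | 10 | 4.0% |
| 30% | 34.3% | 36 | 51.0% | 18.9% | 20 | 9.0% |

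Using all available data discards no interview. It keeps every child except those never seen: d³, or 0.1% at 10% and 0.8% at 20%.

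**Effective sample size under the strict rule.** Assume that the ICC of 0.062 also applies to the interview outcomes and that each kindergarten shrinks in proportion.

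- No loss: 106 / 3.418 = 31.0.
- d = 10%: cluster size 29.2, design effect 1 + 28.2 × 0.062 = 2.75, effective n = 77.3 / 2.75 = 28.1, a loss of 9%.
- d = 20%: cluster size 20.5, design effect 1 + 19.5 × 0.062 = 2.21, effective n = 54.3 / 2.21 = 24.6, a loss of 21%.

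**Bias, as an illustration only.** The simulation has one baseline and one follow-up visit, a true arm difference of zero and 20% missing at follow-up. In one arm, missingness is more likely with a low baseline score (log-odds slope 1 per SD); in the other it is random.

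| Within-child correlation | Complete-case difference, unadjusted (SD) | Conditioned on observed baseline (SD) |
|---|---|---|
| 0.3 | 0.05 | 0.00 |
| 0.5 | 0.08 | 0.00 |
| 0.7 | 0.12 | 0.00 |

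The mechanism and its strength are assumptions. The table shows that the bias is possible and that using the earlier response removes it in this setting.

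**The case against.** The case for leaving the text alone has several parts.

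**Ordinary drafting.** A general sentence followed by a rule for one data source is common, and the Eligibility criteria exclude participants who cannot answer the assessments. This softens the conflict but does not remove it. Using that criterion for a missed later visit would mean excluding children after randomisation according to whether their outcome is available. It would also leave two-visit children undefined.

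**Size.** A reader might take 27% to 49% as the loss the plan causes. The article does not support that as the only figure, because the deletion sentence names only single-visit children, for whom the loss is about 3% to 10%. Nor do raw counts translate directly into lost information in a clustered design. This objection stands, so both readings have to be reported.

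**Validity of complete cases.** It is tempting to say that the planned analysis is valid only if dropout is completely random. That is too strong. Complete-case regression can be unbiased when missingness depends on variables in the model, covariate adjustment is planned, and the simulated bias vanishes once baseline is conditioned on.

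**B against C.** A reader might infer that withdrawal of the reward biases this comparison. Trial design and Implementation show that the reward ends in both groups after the intervention phase; C keeps only the instructions. Reward withdrawal is therefore common to both and gives no reason in itself for differential dropout. A child who misses only the last interview has also been seen twice and is not caught by the single-time-point sentence.

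**The remedy.** The article gives random effects for clustering, in text written for survey and staff data compared after the intervention phase. A child-level longitudinal model is not already planned. Sample size foresees three kindergartens for four groups, so a kindergarten effect is largely confounded with arm. Both points stand. They limit what the remedy can achieve but do not justify discarding observed assessments.

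**Conclusion.** The concern holds for the secondary child interview and observation outcomes: self-efficacy, intrinsic motivation and observed hand hygiene, and with them H4a and H4b. The complete-data rule covers both sources; the single-time-point deletion is worded for the interview. The rules conflict with the inclusion of all eligible participants, leave two-visit children undefined, and discard valid observations for comparisons that the plan itself specifies.

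Under independent missingness of 10% to 20% per visit, which is an assumption, the loss runs from about 3% to 10% of children on the narrow reading to 27% to 49% on the strict one. Even the strict reading costs about 9% to 21% of effective sample size if the pre-study ICC applies. Attrition bias is a risk, not demonstrated, because the article gives neither missingness rates nor mechanisms.

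A reader should not extend the point to the primary outcome. That comes from the washbasin sensors, which collect no person-specific data. The objection is to rules that the article states, not to detail left to an unseen analysis plan. The wording should be changed, but the point does not threaten the main result.

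**What to change.** Replace the complete-data sentence and the single-time-point sentence with one rule. Every child with at least one interview or observation enters a repeated-measures random-effects model with a child random intercept, arm-by-phase terms, and age and gender as covariates. Report the complete-case analysis as a sensitivity analysis, and define complete there (all three visits, or at least two). The general sentence on eligible participants can then stand.

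The cost is two sentences of wording and the specification of a child-level model that the article does not yet contain. No new data are needed: age and gender are already collected.

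The change has limits. The model relies on data being missing at random and would not cure refusal driven by motivation that was never observed. It also does not solve the separate problem that, with very few kindergartens, the cluster effect is largely confounded with arm.
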